## Abstract

**Background:**

In elderly persons frailty and malnutrition are very common and can lead to serious health hazards such as increased mortality, morbidity, dependency, institutionalization and a reduced quality of life. In Austria, the prevalence of frailty and malnutrition are increasing steadily and are becoming a challenge for our social system. Physical training and adequate nutrition may improve this situation.

**Methods/design:**

In this randomized controlled trial, 80 malnourished frail community-dwelling patients (≥ 65 years) hospitalized at wards for internal medicine are recruited. Additionally, 80 lay volunteers (≥ 50 years), named buddies are recruited and subsequently trained regarding health enhancing physical activity and nutrition in four standardized training sessions. These buddies visit the malnourished frail persons at home twice a week for about one hour during an initial period of 10–12 weeks. While participants allocated to the intervention group (n = 40) receive intervention to improve their fluid intake, protein and energy intake, perform strength training and try to increase their baseline activities, the control group (n = 40) only gets home visits without any intervention. After 10–12 weeks, both, the intervention and the control group, receive the nutritional intervention and the physical training. Health, nutritional and frailty status, physical fitness, body composition and chronic inflammation of buddies and frail persons are recorded before the intervention, after 10–12 weeks, 6 and 12 months.

**Discussion:**

To your knowledge this trial is the first of its kind to provide nutritional and physical activity interventions to malnourished frail community-dwelling persons by trained lay buddies, in which an improvement of the frail persons´ and the buddies’ health status is measured. This study assesses the efficacy of such an intervention and may offer new perspectives for the management of frailty and malnutrition.

**Trail registration:**

ClinicalTrials.gov,
NCT01991639

## Background

Frailty is considered as a state of high vulnerability for adverse health outcomes, including disability, dependency, falls, need for long-term care and mortality
[1]. Moreover, other difficulties regarding frailty include morbidity, hospitalization, social isolation and an overall decrease in quality of life
[2]. According to the Frailty Instrument for Primary Care of the Survey of Health, Ageing and Retirement in Europe (SHARE-FI)
[3], the prevalence of frailty in persons older than 65 years is 17%. Additionally, 42.3% are pre-frail, which is an intermediate state between being robust and frail. In Austria, the prevalence of frailty is 10.8%, pre-frailty appears in 40.7% of community-dwelling older people
[4]. Through extrapolation of the predicted demographic development, a number of 356,000 frail and 1.5 million pre-frail persons may be expected in 2050 in Austria
[5]. Due to this epidemiologic trend, treatment and especially prevention of frailty is becoming one of the greatest challenges for our social system.

Sarcopenia, which is defined as reduced muscle mass and strength and impaired muscle performance
[6], significantly contribute to the development of frailty
[7]. Underlying reasons for sarcopenia are the ageing process, heritability, an unbalanced diet, a sedentary lifestyle and chronic diseases
[8-10]. Within the existing literature, the prevalence of sarcopenia in 60 to 70-year old people is between 5–13%
[11] and in the population aged 80 years or older it increases to 11–50%
[6].

In addition, malnutrition is associated with a higher risk of becoming frail and it contributes to its pathogenesis
[7,12-14]. It is defined as a chronic state in which a combination of over- and undernutrition and inflammatory activity modifies the body composition
[15,16] and consequently may lead to serious health hazards
[17-22]. According to a review by Guigoz et al. the prevalence of malnutrition in hospitalized patients is 23% and 46% are at risk of malnutrition, respectively
[23].

Furthermore, chronic inflammation parameters e.g. leukocytes, interleukin 6 (IL-6), tumour necrosis factor (TNF-alpha)
[24,25] and c-reactive-protein (CRP)
[24-26] are associated with both, malnutrition and frailty. Moreover, deficits in vitamin D, with its benefit on bone, muscle, and nerve function
[27], could be a sign of malnutrition
[28,29]. In addition, low levels of serum proteins e.g. albumin and transferrin, and of total cholesterol and triglycerides might indicate malnutrition
[30].

As nutritional and frailty status frequently deteriorate post-discharge
[31], it can be concluded that energy and especially protein intake must be improved in frail malnourished elderly persons who are still living at home. An individualized nutritional counseling, which takes place three times at patients’ home after discharge, and is conducted by registered dietitian has the potential to improve the nutritional status within 12 weeks
[32]. Moreover, exercise training, especially strength training, can improve health status and quality of life
[33,34]. According to the fact that a lack of strength is one of the major cause of falls and consequences in frail persons
[35-37], strength training may empower elderly people to maintain or regain autonomy and independency. Therefore, a home-based well-structured nutritional intervention program in combination with strength training can be considered as an effective therapeutic option for the treatment of frailty
[38] and malnutrition. Due to this intervention the negative outcomes of frailty and malnutrition are expected to be reduced and should help older persons to maintain or even improve their quality of life. Additionally, the general well-being, muscle strength, and activities of daily living are expected to improve
[39].

## Methods/design

### Overview

The proposed study is designed as a prospective randomized controlled trial taking place in Vienna, Austria. A randomization design, which is stratified by handgrip strength, is chosen to get two comparable groups of participants in the intervention and the control group. In the study 80 community-dwelling malnourished frail persons are recruited. They are visited by buddies (volunteers ≥ 50 years) twice a week for about one hour for 6 months. An overview of the study design and the assessment points is provided in Figure 
1.

**Figure 1 F1:**
[figure not shown]
Study design and assessment points.

The study was approved by the local ethical committee of the Medical University Vienna (Ref: 1416/2013) and complies with the Declaration of Helsinki
[40]. Furthermore, the protocol was registered at clinicaltrials.gov (Identifier: NCT01991639). The study methods are in accordance with the CONSORT guidelines for reporting randomized trials
[41].

### Pre-studies

The methods presented in this study are built upon two pre-studies. The findings of the first pre-study illustrated that 54.13% of people over the age of 65 years (n = 133) inpatient in the ward for internal medicine in acute hospitals in Vienna are frail and 25.56% are malnourished. Additionally, even more are at higher risk (pre-frail: 21.8%; at risk of malnutrition: 51.13%)
[39,42]. Moreover, this pre-study showed that 64.7% of the participants are willing to improve their health situation and they are interested in a home-based program (64.7%), which is based on strength training and improvement of nutritional habits.

The second pre-study by Müller et al. proved that with the help of the Austrian charitable organizations it is possible to recruit a sufficient number of volunteers, who are willing to perform and supervise the exercise program and the nutritional intervention. Furthermore, in this pre-study the buddies were trained and educated in a one-day workshop. After one month their knowledge and skills concerning the most important aspects of healthy nutrition and exercise training were tested. The results of this pilot study showed that with an extensive preparation lay people, older than 50 years, are certainly capable to conduct these interventions
[43]. However, a several-day workshop should be preferred to train the buddies.

### Study objectives

The primary objective of the study is to increase the handgrip strength by this intervention, measured with a dynamometer. Further aims of the proposed study are to improve the nutritional status, to increase the amount of health enhancing physical activity and to improve the overall health status in malnourished frail community-dwelling older people and buddies.

Due to the project design, the social networks and social interaction of buddies and frail person is expected to be strengthened. In addition, health resources and quality of life should be increased.

A clear objective of this study is to perform the nutritional and physical training intervention in malnourished frail people’s home environment.

### Recruitment and eligibility

#### Malnourished frail persons

Malnourished frail people 65 years and older, who are inpatient in five hospitals in Vienna, wards for internal medicine, and close to discharge are recruited in four waves within one year. The inclusion and exclusion criteria for malnourished frail persons are shown in Table 
1.

**Table 1 T1:** Inclusion and exclusion criteria of frail malnourished persons

**Inclusion criteria**	**Exclusion criteria**
▪65 years or older	▪Planned admission to nursing home
▪Resident in Vienna	▪Chemo or radiotherapy at the moment or planned
▪Malnutrition or at risk of malnutrition according to the MNA-SF (≤ 11 points) OR	▪Nursing level 6^a^ or 7^b^
Frail or pre-frail according to the SHARE-FI (female: >0.315; male: >1.212 points)	
▪Community-dwelling	▪Insulin treated diabetes mellitus according to the medical charts
▪No medical contraindication for the performance of strength training (“No” to the question ‘Has your doctor recently told you that you should not exercise?”)	▪COPD stage III or IV
▪Able to walk (with or without a walking aid)	▪Dialysis patient or chronic kidney insufficiency with protein restriction
▪Capability to consent	▪Cannot understand the German language
	▪Impaired cognitive function according to the MMSE (≤ 17 points)

^a^more than 180 hours of care is necessary; care cannot be planned or is permanently required.

^b^more than 180 hours of care is necessary; person cannot move without help.

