### Randomization

Persons are randomly assigned to the intervention or control group, stratified by handgrip strength with the help of the “Randomizer for Clinical Trials 1.8.1″
[45]. Randomization is carried out after the patient has signed the informed consent and has been matched to a lay buddy, dependent on the place of residence.

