### Control group

Participants in the control group are visited twice a week by buddies, but they do not specifically monitor the nutritional status or perform physical training in the first 10–12 weeks. Instead of that, buddies are provided with a portfolio of possible activities, especially cognitive training, which they could perform together with the frail malnourished person. After 10–12 weeks the control group also receives nutritional intervention and the physical training for 3 months.

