#### Activities for improving nutritional habit

The aim is to obtain adequate protein, energy and other nutrient intake, preferably by regular foods and beverages. Therefore, buddies discuss the following three main nutritional messages with the malnourished frail persons: fluid intake**,** animal and plant protein intake and energy intake. For this purpose, buddies are equipped with a portfolio in which the topics concerning physical activity and nutrition are explained in a straightforward manner. Moreover, they obtain ideas how to enrich food with protein and receive recipes of dishes which are protein and energy dense.

In order to show the variance of recommended and actual food intake, buddies are equipped with the “Healthy for Life Plate” which is a modification of the Health Eating Plate of the Harvard University
[46]. It consists of a play board and food-cards representing a variety of foods (Figure 
2).

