**Figure 2 F2:**
[figure not shown]
Healthy for life plate.

One food-card shows one portion size. Buddies and malnourished frail persons should set these food-cards, which they have eaten the day before, on the play board. The “Healthy for Life Plate” assesses the quantity and the composition of daily food rations. Therefore, with the game, dietary behavior can be examined and consequently optimize dietary habits. For convincing malnourished frail persons to change their nutritional habits, buddies additionally use motivational interviewing techniques
[47]. Due to this fact every nutritional message includes a section for individual goal setting and tools to reinforce the self-efficacy. As it is done in the motivational-volitions-concept
[48], every message also includes a part which should reveal problems of implementing the goal in everyday life, in order to find solutions for them.

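### Table 1 screens for medical limits on exercise and on protein but not for a prescribed fluid restriction, although fluid intake is one of the three messages lay buddies deliver

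*Protocol article*

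**What the plan says.** The section on recruitment and eligibility presents Table 1 as the inclusion and exclusion criteria. The population is people aged 65 or older on internal-medicine wards who are close to discharge. Three entries matter here:

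- For the exercise component: "No medical contraindication for the performance of strength training", checked by one question about a doctor's recent advice.
- For diet: "Dialysis patient or chronic kidney insufficiency with protein restriction".
- For the source of information: "Insulin treated diabetes mellitus according to the medical charts", which shows that the chart is already consulted at screening.

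The abstract says that intervention participants "receive intervention to improve their fluid intake, protein and energy intake". The section on nutritional habits says that "buddies discuss the following three main nutritional messages with the malnourished frail persons: fluid intake", followed by protein and energy. The same section adds that "every nutritional message includes a section for individual goal setting", and that buddies use motivational interviewing. Under Control group, after the initial 10–12 weeks, "the control group also receives nutritional intervention and the physical training for 3 months".

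Table 3 records comorbidities and long-term medication at Selection. Any symptom or disease during the intervention counts as an undesirable event; the nutritional and exercise units then stop and the participant must see a physician.

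**The concern.** The plan accepts that a doctor's restriction can make a component unsuitable for a given person. It screens for such a restriction on the training, and it excludes kidney patients whose protein is restricted. The fluid message has no counterpart in the same table.

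At stake is participant safety. Someone sent home from an internal-medicine ward with a fluid limit could agree on a drinking goal with a volunteer who does not know of that limit. The Discussion describes the buddies as non-professionals, so they cannot be expected to find the conflict without being told.

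**Working it through.** No figure in the plan bears on this point, so the check compares the components with the screen and then follows one patient through the described steps.

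**1. Component against screen**

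| Component | Medical limit screened in Table 1 |
|---|---|
| Strength training | Yes: contraindication question |
| Protein message | Yes, for kidney disease: insufficiency with protein restriction; dialysis |
| Energy message | No prescribed restriction named; insulin-treated diabetes is excluded, without a reason given |
| Fluid message | None named; dialysis and protein-restricted kidney disease remove some candidates indirectly |

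The kidney criterion depends on protein or dialysis. A fluid restriction that comes with neither is not caught.

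**2. One patient traced through the plan**

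Take a 75-year-old Vienna resident who is at risk of malnutrition, walks with an aid, can consent, has an MMSE above 17 and meets none of the listed exclusions, but has a prescribed fluid limit.

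- *Eligibility:* every inclusion criterion is met and no exclusion applies, so the person is enrolled.
- *Selection records:* comorbidities and medication are noted, but no action is tied to them, and nothing says that buddies are informed.
- *Buddy training:* 4 sessions × 3 h = 12 h. The listed topics do not include prescribed dietary or fluid limits.
- *Delivery:* the fluid message and its goal are discussed at home.
- *Follow-up meeting with the team:* two to three weeks after the start. At two visits a week, 2 × 2 = 4 to 2 × 3 = 6 visits are planned by then.
- *Undesirable-event rule:* it acts only after a symptom or disease has appeared.

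No stated step brings the restriction to the buddy's notice before the message is given.

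**3. Reach**

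Offered the nutritional intervention as planned: 40 (intervention, from the start) + 40 (control, after 10–12 weeks) = 80. This is an upper bound on those who hear the fluid message, because the number of messages actually discussed is an adherence measure. The share of the 80 with a prescribed fluid limit is not in the article, so no count of affected persons is given.

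**The case against.** The best case against has four parts.

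- *Condensed article.* A caution to buddies would normally sit in the portfolio, the guidebook or the full protocol, none of which is shown. This stands for delivery instructions, so their absence here is no finding. It does not reach the eligibility table, which is printed and described as the criteria.
- *No stated conflict.* The article gives no volume or minimum intake. Goals are individual, and each message includes a part for finding obstacles and solving them. A goal can therefore respect a limit. That is correct, but it requires the buddy to know of the limit.
- *General safeguards.* Participants can consent and may report a doctor's order; a physician is on the team that trains the buddies; comorbidities and medication are recorded; symptoms stop the units. These help. None is stated to cover fluid, and the event rule and the follow-up meeting come after visits have begun. Self-report is a weak sole safeguard where only MMSE scores of 17 or lower are excluded.
- *Unknown size.* The article does not mention fluid restriction or how common it is in this population. This stands in full and limits how much weight the point can bear.

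A reader might infer that the plan contradicts itself, that volunteers are told to push fluids against medical advice, or that all 80 participants are at risk. The article supports none of these. Its aim is an improved intake with individual goals, and 80 is only the number offered the intervention.

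**Conclusion.** The point holds for the eligibility and selection screen: Table 1 covers medical limits on the exercise component and, for kidney disease, on the protein message, but not a prescribed fluid restriction outside dialysis and protein-restricted kidney insufficiency. The fluid message nevertheless goes to both arms over time.

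It is a gap and a modest safety improvement. It rests on one clinical assumption that the article does not document: that some patients discharged from these wards have such a restriction. The number affected and the strength of any conflict are unknown, and materials not shown may already warn buddies. A reader might suspect that the handgrip comparison is compromised. Nothing in the article supports that, and no effect on the estimand, the sample size or the analysis is claimed.

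**What to change.** At Selection, read any prescribed fluid restriction from the medical chart, as is already done for insulin-treated diabetes. Do this before allocation and identically in both arms. The existing sequence allows it, since "Randomization is carried out after the patient has signed the informed consent" and the match to a buddy has been made.

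For the persons identified:

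- omit the fluid message or keep it within the prescribed limit;
- tell the buddy before the first visit in the intervention arm, and at the refresher training before the control arm starts the intervention;
- keep them in the trial and analyse them as randomised.

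Because the restriction is recorded before randomisation, identifying these persons cannot depend on allocation.

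The alternative is to add medically prescribed fluid restriction to the Table 1 exclusions. This is simpler to run, but it removes people who could still receive the training and the other two messages.

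The cost is one chart item and one instruction within buddy training that is already planned. The downside is that a few participants receive two of the three messages or, under the alternative, a few are excluded.

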#### Buddies

The buddies are recruited in cooperation with the “Wiener Hilfswerk” in four waves within one year. The “Wiener Hilfswerk” is one of the largest organizations in Austria, which already offers care-giving services for elderly persons carried out by volunteers. The inclusion criteria for buddies are:

• 50 years or older

• Readiness to participate in the study either in the intervention or control group

• Commitment to keep to the protocol for at least 6 months

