#### Physical intervention

Twice a week strength training is performed by malnourished frail persons together with the buddies. The training comprises a warm-up (about five minutes, mobilization exercises) followed by six strength exercises, which are performed in circuit form with two sets. The exercises are conducted with 15 repetitions until muscular exhaustion. The performed exercises can be retained from Table 
2. This circle lasts about 30 minutes. Moreover, buddies talk about the relevance of health enhancing physical activity in connection with frailty. Further on, they discuss possible arising problems, talk about their baseline activity and set individual goals concerning physical activity. For personal motivation buddies and frail people get a pedometer. Additionally, buddies advise the malnourished frail elderly to practice the same strength exercises once a week on their own.

**Table 2 T2:** Description of the six strength exercises

**Basic exercise**	**Alternative exercise**	**Muscle group**
▪Mini squat in front of a chair (with the help of a table)	▪Lunges	▪Femoral muscles
▪Chest Press against elastic resistance - sitting on a chair	▪Chest Press against the wall	▪Pectoral muscles
▪“beetles” - sitting on the chair		▪Abdominal muscles
▪Hip extension - standing position	▪Hip extension - standing position against elastic resistance	▪Ischiocrural muscles
▪Reverse Butterfly against elastic resistance - sitting on a chair		▪Upper back muscles
▪Shoulder press against elastic resistance - sitting on a chair		▪Muscles of the arms, and shoulders

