• *Muscle strength* assessed by the MASS (Measurement of age and sex related reference values of muscle strength) and the Concept 2 Dyno. The MASS is a new diagnosis system which was developed by the Technical University of Vienna. It evaluates health related concentric dynamic muscle strength. The measurement is velocity-independent and hence, is appropriate for the target group. Three exercises (bench press, bench pull, and leg press) will be conducted in standardized procedure. For all tested muscle groups the following parameters are recorded: maximum resistance with low velocity and 2–3 fix adjusted sub-maximum loads. Moreover, the Concept 2 Dyno is used for assessing the muscle strength. The same exercises as before will be conducted in standardized procedure
[63].

• *Daily physical activity* assessed by an activity sensor (pedometer), the modified PASE (Physical Activity Scale for the elderly)
[64] and the modified questionnaire on health-related behavior FEG (Fragebogen zur Erfassung des Gesundheitsverhaltens)
[65]. The pedometer-data will be analyzed as follows: Data from the week before AP2, AP3 and AP4 will be included in the analysis. Data of those who have used the pedometer less than four days are excluded. Days, on which the pedometer was used less than eight hours, are considered as invalid. The number of steps below 90 steps per minute, the number of steps above 90 steps per minutes and the walk time is analyzed.

• *Balance and mobility components* assessed by the SPPB (Short Physical Performance Battery)
[66].

• *Laboratory parameters* for malnutrition or frailty (albumin, total cholesterol, transferrin, triglyceride, 25-hydroxy-vitamin D, folic acid, CRP, IL-6, TNF-alpha and leucocytes)

Other measurements

• *Personal data* e.g. age, gender, family status, education level, income, occupation

• *Measures of drop-out (DO)*[67]*:* the drop-out rate between the first and second visit and until the final visit should be analyzed. For each case of discontinued participation (Ri), the following reasons are discriminated: medical reason (R1) and person’s own decision (R2), whereas an “A” stands for all participants who passed the baseline assessment.

• Drop-outs between the first and second visit:

⋅DO_R_ = DO_1_ + DO_2_ – all participants who drop out between the first and second visit

⋅DO_R1_ = DO_1_/A – percentage of participants who discontinue by medical reasons.

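### Buddies do the strength training and the strength tests, but their entry criteria, unlike those for the frail persons, contain no exercise-contraindication check

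*Protocol article*

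**What the plan says.** **Who may be a buddy.** Under Recruitment and eligibility, the Buddies subsection opens with "The inclusion criteria for buddies are" and gives three items: "50 years or older", "Readiness to participate in the study either in the intervention or control group" and "Commitment to keep to the protocol for at least 6 months". No exclusion criteria and no upper age limit are printed for buddies.

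**Who may be a frail participant.** Table 1 lists inclusion and exclusion criteria. One inclusion item is "No medical contraindication for the performance of strength training", settled by a single question on whether a doctor has lately advised against exercise.

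**What buddies do.** The Physical intervention subsection states: "Twice a week strength training is performed by malnourished frail persons together with the buddies". The session has six exercises in two sets, and "The exercises are conducted with 15 repetitions until muscular exhaustion". Under Training of the buddies, the project team exercises with them to demonstrate each movement and its intensity.

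**How buddies are tested.** Table 3 marks MASS for frail persons and buddies at AP1, AP2 and AP3, and the Concept 2 Dyno for buddies only at the same three points. The Measurements section says that MASS uses bench press, bench pull and leg press and records "maximum resistance with low velocity and 2–3 fix adjusted sub-maximum loads".

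**The concern.** Two groups do the same strength training. One is asked before entry whether a doctor has advised against exercise; the other is not. The group that is not asked takes both strength tests, whereas the frail persons take only one of them.

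The stake is the safety of the volunteers. Someone with medical advice against exercise satisfies all three buddy criteria. The third criterion then commits that person to at least six months of a protocol that includes exercise to exhaustion and strength testing. Buddies are also study subjects and not only providers of the intervention: the Study objectives section names improvement of their health as an aim, and they are assessed at the same four points as the frail persons.

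**Working it through.** No figure in the article bears on this point. The sample size concerns handgrip strength in frail persons and would not change if buddies were screened. The check is therefore a comparison of the relevant sections.

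**1. Do buddies exercise, or only supervise?** The training description could be read as supervision, because the frail persons are the ones named as performing it. Three other places settle the matter:
- The Discussion calls it crucial that both parties perform the strength exercises regularly and at the right intensity.
- The adherence measures count activity units that one partner does without the other.
- The buddy training sessions include exercising with the project team.

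**2. When are they exposed?**

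| Activity | Intervention-arm buddies | Control-arm buddies |
|---|---|---|
| Exercise in the buddy training sessions | Before home visits begin | Before home visits begin |
| MASS and Concept 2 Dyno | AP1, AP2, AP3 | AP1, AP2, AP3 |
| Home strength training with the partner | From the start | Only after the first 10–12 weeks |

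Buddies are assessed after their last training session, so the exercise in those sessions comes before the AP1 tests.

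**3. Which entry rule covers that exposure?**

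| Eligibility item | Frail persons (Table 1) | Buddies |
|---|---|---|
| Minimum age | 65 | 50 |
| Exercise-contraindication question | Yes | None |
| Any other health item | Several exclusions | None |

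Readiness for either arm and commitment to the protocol are statements of willingness. Neither is a medical check.

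**4. Does any other rule close the gap?** The only other relevant safeguard is the undesirable-event rule, which requires exercise to be suspended and a physician to be seen. It acts only after an event has occurred, so it cannot serve as an entry check.

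**5. How many people?** There are 80 buddies and 80 frail persons, so buddies are 80/160 = 50% of those recruited. All 80 are due to exercise in training and to be tested at AP1. With 40 couples per arm, 40 buddies do home training in the first 10–12 weeks, and the other 40 start after that period.

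**The case against.** The strongest objection is that this is a journal article. It prints no exclusion criteria for buddies at all, and the full protocol approved by the ethics committee, or the volunteer organization, may screen them. That possibility stands, and it is why the fix offers two routes. It does not remove the point. Buddy eligibility is printed as an explicit list, and the same article prints the check for the other group that exercises. Followed as written, the list admits a volunteer who has been told not to exercise.

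Some mitigating facts also stand. A medical doctor belongs to the team that trains the buddies over four three-hour sessions. The home exercises are seated, standing or elastic-resistance movements. The criteria make clear that buddies must be ready to serve in the intervention arm. None of these is an entry check.

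A reader might go further and infer that a buddy who has to stop exercising ends the couple's training, costs the arm one of its 40 participants and so endangers the primary result. The documents do not support this:
- Nothing says that training ends when a buddy stops exercising. Such a buddy might still visit and instruct, and the frail person has a guidebook and a DVD and is advised to train once a week alone.
- The primary endpoint is the frail person's handgrip strength, analysed by intention to treat, so a buddy's withdrawal from exercise does not remove that person from the analysis.
- The increase from 36 to 40 per group is justified by the effect of drop-out imputation on the standard deviation. It is not an allowance for buddies who stop.
- Control-arm couples do no home training in the first 10–12 weeks, which is the period of the primary comparison.

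A reader might also take both strength tests to be maximal. The article uses that term only for MASS; for the Concept 2 Dyno it says that the same exercises are done in a standardized way.

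**Conclusion.** The point holds as an inconsistency between two eligibility lists and as a participant-safety gap. A volunteer advised against exercise meets every printed buddy criterion, while a frail person who reports the same advice is barred. Up to 80 buddies are exposed, with control-arm buddies joining the home training only after the first 10–12 weeks.

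The article gives no rate of contraindications among volunteers, so the number actually at risk is unknown; the finding does not depend on it. The conclusion assumes that the printed list is the operative rule for enrolling buddies. If screening exists in a document not shown, what remains is that the published criteria omit it. No effect on the primary comparison is claimed. The change is worth making because it protects participants at very little cost.

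**What to change.** Reconcile the buddy criteria with Table 1 and with the sections on physical intervention, buddy training and measurements, by one of two routes:
- Extend the existing Table 1 contraindication item, with its single question, to buddies. Ask it at recruitment, before the first training session and therefore also before the AP1 strength tests.
- If buddies are already screened elsewhere, state that criterion in the buddy list.

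The cost is one question already in use and a one-line amendment. A few volunteers may be turned away, which could slow recruitment slightly. The intervention, the schedule of assessments and the sample-size inputs do not change.
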